### Criteria for discontinuing or modifying allocated interventions {11b}

The intervention will be discontinued if the participant, for any given reason, does not complete the planned 20–25 sessions. In such an event, the participant will be invited to remain in the study and continue the follow-up visits to harvest the non-training data.

### Relevant concomitant care permitted or prohibited during the trial {11d} and provisions for post-trial care {30}

All participants will receive usual care at the clinics throughout the trial. Standard care is provided within the Norwegian health care system.

## Outcomes {12}

### Primary outcome

The primary endpoint is the change in working memory function after 6 months measured by Spatial Span Backwards (from the Wechsler Memory Scale, third edition (WMS-III)) [39, 40].

To investigate immediate and long-term effects, the intervention groups will also be compared to the active control at 3, 12, 24, and 48 months. We will investigate a possible dose-dependent effect by comparing working memory performance, measured by spatial span backwards at 6, 12, 24, and 48 months, between the group receiving two periods of working memory training and the group receiving one period.

### Secondary outcomes

#### Clinical outcomes

Secondary cognitive endpoints are scores on tests within the working memory domain at 3, 6, 12, 24, and 48 months post intervention assessments. Moreover, secondary endpoints are the RBANS composite score, scores on the executive function domain, scores on the Mini-Mental State Examination (MMSE), the Clinical Dementia Rating scale (total and sum of boxes), and conversion to dementia.

We consider the participants as having dementia when they fulfill the National Institute on Aging and Alzheimer’s Association (NIA-AA) 2011 criteria for all-cause dementia [41]:

Cognitive or behavioral symptoms that:Hinder the ability to function independently in activities of daily living or workConstitute decrease in functioning and performing from previous levelsCould not be explained by delirium or a major psychiatric disorderCognitive impairment detected through history taking and cognitive testingInvolves at least two of the following domains:Immediate learning and delayed memory (list learning, story memory, list recall, list recognition, story memory and figure recall index score from RBANS test battery)Reasoning, judgement and handling of complex tasks (Clinical Dementia Rating Scale, CDR).Visuospatial abilities (figure copy and line orientation index score from the RBANS test battery)Language (picture naming and semantic fluency index score from RBANS test battery)Behavioral and psychological symptoms (Neuropsychiatric Inventory Questionnaire (NPI-Q), and Mild Behavioral Impairment Checklist (MBI-C))

We require age- and education-adjusted scores at least 1.5 SD below the mean to consider a cognitive domain as affected. Affected behavior requires a minimum of one domain with the severity score 2 (moderate) or 3 (severe) or a NPI-Q sum score ≥ 3. To ensure consistency, dementia diagnoses will be discussed in consensus meetings involving experienced geriatricians and neuropsychologists.

#### MRI

The effects of working-memory training on cerebral white-matter microstructure will be measured by quantitative magnetic resonance imaging (MRI) (Work package 1).

Investigate WM-training effects on gray matter evaluated by quantitative MRI techniques (Work package 2).

Assessment of ASL as a predictor of trainability in MCI patients (Work package 2).

#### High responders/subgroups (work package 2)

We will perform subgroup analyses on differences in training effects to identify high responders according to:oAmnestic MCI and non-amnestic MCIDifferent etiologies of MCIThe presence of amyloid, tau or neurodegenerationAllelic variations in APOE, LMX1a, COMT, AQP4, and AQP4 AU allelesCerebral white and grey matter evaluated by quantitative MRI techniquesAssociation with QSM values attained by MRIFrailtySleep qualityNeuropsychiatric symptoms

Furthermore, in the glymphatic sub-study we will assess the influence of the glymphatic system by testing how the craniospinal clearance rate is associated with working memory function and training effect. Parameters of craniospinal clearance function, including absorption half-life (T1/2, abs), time to maximum concentration (Tmax), and lag-time of absorption to blood (Tlag), were used as surrogate markers of brain glymphatic clearance function, since previous studies have shown a high association between CSF clearance and brain clearance. The clearance parameters are based on previous pharmacokinetic modeling studies.

#### Quality of life and relatives stress (work package 3)

Participant and relative quality of life (QoL), as well as relative stress, will be measured at baseline and at 3, 6, 12, 24, and 48 months post-intervention.

The next-of-kin completes the Relative stress scale (RSS), a self-administered questionnaire assessing various aspects of proxy distress divided into the subscales “emotional distress,” “social distress,” and “negative emotions.”

QoL of participants and their next-of-kin will be assessed, with EQ-5D-5L, at baseline and at 3, 6, 12, 24, and 48 months post-intervention. Additionally, participants and their next-of-kin will complete the BRIEF-A at the aforementioned intervals. The BRIEF-A assesses executive function and self-regulation in daily life, covering two main indexes (metacognition and behavioral regulation), along with an overall summary score and three validity indicators. The BRIEF-A provides an indirect measure of QoL and relative stress, by assessing how executive function impacts daily life of the participants.

The combination of RSS, EQ-5D-5L, BRIEF-A, in addition to the Neuropsychiatric Inventory Questionnaire ensures solid information on QoL and relative stress.

#### Use of health care resources and health economics (work package 4)

A cost-utility analysis will be performed to evaluate if the working memory training is more cost-effective compared to the active control group in the MCI phase. The generic outcome in the analysis is QALYs derived from the instrument EQ-5D 5L. The secondary outcome is productivity loss of relatives and patients.

The use of QALY as a patient-reported outcome measure in dementia research is debated, as concerns arise regarding patients’ potential unawareness of their impairments or difficulty accurately reporting their status due to memory limitations. The health economic analysis will therefore include the following costs:Intervention-related costsDirect costs/health care costs, mainly related to the use of health care services, including primary, secondary and tertiary care and health servicesIndirect costs, including work absence for the patients and the relatives of the patients (i.e., productivity loss).

Data will be collected through self-report measures (EQ-5D 5L) and from the Norwegian patient registry. Informal care will be measured by interviews with the family using Resource utilization in dementia [42].

### Participant timeline {13}

See Fig. 1 for the participant’s timeline through the trial.

### Sample size {14}

Sample size and power estimations are based on previously published data [43], assumed effect sizes (Cohen’s *d*) in the study population, and a comparison of two groups with equal sample sizes for simplicity. Stata 15 was used for the estimations, assuming an 80% power (beta = 0.8) and a 5% significance level (alpha = 0.05).

Work package 1: A comparable study reported a mean Spatial Span Backwards score of 5.80 (SD 2.00) at baseline in MCI [43]. A clinically significant effect between groups is defined as a mean difference of 0.5 times the standard deviation, resulting in a required sample size of 64 participants per group. With three groups, this totals 192 participants. Accounting for an anticipated 10% dropout rate, we plan to include a total of 213 (71 in each group).

Work package 2: Genetic variation and craniospinal clearance rate may independently influence or modify the effect of working memory training. The planned sample size is adequate to detect an effect comparable to the expected intervention effect, defined as a mean difference of 0.5 times the standard deviation. We should be able to assess possible effect modification within the intervention groups if it is strong (a Cohen’s *d* population parameter of about 1.0).

Work package 3: A comparable non-dementia study sample reported a mean RSS score of 6.6 (SD 8.8) [44]. Although no minimal clinically important difference has been established, we assume a similar mean difference between groups as estimated for the primary outcome in work package 1 (i.e. Spatial Span backwards score). Thus, the planned total sample size of 213 participants (71 in each group) is considered sufficient.

Work package 4: Assuming an annual dementia transition rate of 9.6% [3], a study population of 213 individuals is projected to yield 39 cases of dementia at the 24-month follow-up and 71 cases at the 48-month follow-up. However, these estimates are affected by uncertainties regarding the transition rate specific to working-memory-training populations and the applicability of international data to a Norwegian cohort.

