### Objectives {7}

The primary objective of the present study is to evaluate the overriding hypothesis that working memory training is an efficient and cost-effective intervention in MCI as compared to an active control group. To test this hypothesis, we have formulated four aims, giving rise to four work packages.

Work package 1: We aim to investigate if a single period of working memory training is sufficient to achieve effects on cognitive function after 6 months measured by spatial span backwards. To assess potential transfer effects, we will further examine whether working memory training impacts memory, attention, visuospatial abilities, language, executive function, or behavior (neuropsychiatric symptoms) are impacted by training. Moreover, we will investigate a possible dose-dependent effect of working memory training by comparing the group receiving two periods of working memory training with those receiving one period. Microstructural effects of working memory training on cerebral white matter after 6 months measured by quantitative magnetic resonance imaging (MRI) will be explored. We will perform subgroup analyses on difference in training effects between amnestic MCI and non-amnestic MCI, according to different etiologies of MCI, and according to the presence of amyloid, tau or neurodegeneration.

Work package 2: The aim is to investigate possible characteristics of high responders of working memory training regarding demographic and clinical factors and allelic variations in LIM homeobox transcription factor 1 alpha(*LMX1a*), Catechol-O-methyltransferase (*COMT*), Apolipoprotein epsilon (*APOE*), Aquaporine 4 (*AQP4*), Aquaporine 4 anchoring protein (*AQO4*). The influence of the glymphatic system will be examined by testing how craniospinal clearance rate is associated with working memory function and training effect. Lastly, in work package 2, we will investigate working memory training effects on gray matter evaluated by quantitative MRI techniques.

Work package 3: The aim is to investigate if working memory training impacts quality of life (for both participant and proxy) and relative’s stress.

Work package 4: The aim is to evaluate whether working memory training is cost-effective in MCI. The quality adjusted life years (QALY) associated costs and the use of health care resources in the patient and relative population will be investigated in the MCI study population as a whole and by training group.

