## Statistical methods

### Statistical methods for primary and secondary outcomes {20a} and subgroup analyses {20b}

Baseline characteristics and other descriptive data will be summarized using appropriate descriptive statistics. Continuous variables will be described using the mean and standard deviation, or the median and interquartile range, as appropriate based on the distribution. Categorical variables will be described using counts and percentages. Simpler parametric or non-parametric comparisons may be used for descriptive or supplementary analyses.

The main analytical framework for longitudinal primary and secondary outcomes will be regression-based repeated-measures analyses, primarily using linear mixed-effects models (LMEs) (and generalized mixed-effects models for non-continuous outcomes, where relevant). These models account for within-participant correlation over time and allow inclusion of participants with incomplete follow-up data under standard model assumptions. Analyses of intervention effects will include time, treatment group, and the time × treatment group interaction as key terms. Relevant covariates (e.g., age, sex, and baseline values), as appropriate for the specific outcome, will be included in adjusted analyses. Given the heterogeneity of disease severity in MCI and risk of baseline imbalance in a moderate sample size, if systematic baseline differences are observed across the groups, a multidimensional composite covariate may be developed and included as an adjustment variable.

Planned contrasts will include comparisons of the single-training group and double-training group versus the active-control group at 6 months as the main outcome. If the double-training group is significantly better than the active-control group at 6 months, the estimated mean difference between the double-training and single-training groups will be tested at the 5% significance level to assess a possible dose–response effect. Pairwise contrasts between groups will also be estimated at 3 and 12 months to assess immediate and longer-term effects. Multiple comparisons will be applied using Holm–Bonferroni across the relevant tests. Results will include estimated marginal means with 95% confidence intervals, mean difference between groups with 95% CIs, and standardized effect sizes (Cohen’s *d* derived using the pooled baseline standard deviation).

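### The stated 80% power is for one two-group test at 5%; under the planned Holm rule the same assumptions give about 72% to 77% per primary contrast

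*Protocol article*

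**What the plan says.** **Sample size {14}.** The calculation rests on "a comparison of two groups with equal sample sizes for simplicity". The target effect is set as follows: "A clinically significant effect between groups is defined as a mean difference of 0.5 times the standard deviation". With the cited SD of 2.00 for Spatial Span Backwards, that is 1.0 point. Power and alpha are given as "assuming an 80% power (beta = 0.8) and a 5% significance level (alpha = 0.05", "resulting in a required sample size of 64 participants per group". Three groups make 192, and an expected 10% dropout brings the total to 213. The section mentions neither a second primary contrast nor any division of alpha.

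**Statistical methods {20a}/{20b}.** "Planned contrasts will include comparisons of the single-training group and double-training group versus the active-control group at 6 months as the main outcome". If double training beats control at 6 months, double versus single is then tested at 5%. Contrasts at 3 and 12 months follow, and then: "Multiple comparisons will be applied using Holm–Bonferroni across the relevant tests".

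**Objectives {7}.** Work package 1 asks "if a single period of working memory training is sufficient to achieve effects on cognitive function after 6 months".

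**The concern.** With two primary contrasts, Holm compares the smaller p-value with 0.025 and, only if that succeeds, the larger with 0.05. A calculation at "5% significance level (alpha = 0.05" with no split therefore describes an easier test than the one planned.

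Power per contrast matters here. The first objective concerns single training specifically, and the dose-response test opens only if double training beats control. If the 80% stands unqualified, readers of a non-significant result for either regimen will judge it against a higher power than the sizing assumptions support.

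**Working it through.** **Inputs.** From Sample size {14}: d = 0.5, SD = 2.00, n = 64 evaluable per group, alpha = 0.05, power 80%, dropout 10%. From Statistical methods: two 6-month contrasts sharing one control group, under Holm. Sidedness is not stated. Two-sided is assumed because a two-sided t-test reproduces 64, while a one-sided test gives 50.

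**Step 1: reproduce the article's figure.** For a two-sample t-test with 2n − 2 = 126 degrees of freedom, the noncentrality is d × √(n/2) = 0.5 × √32 = 2.83.
- At two-sided 0.05 the critical value is 1.98 and power is 80.1%. The figure of 64 reproduces.
- 64 × 3 = 192, and 192/0.9 = 213.3, against 213 stated.

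**Step 2: the first Holm step.** At two-sided 0.025 the critical value is 2.27. The same noncentrality gives 71.2%.

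**Step 3: the full Holm procedure.** Three-arm trials were simulated with 64 per group, a shared control and a pooled three-group variance (189 degrees of freedom). A contrast counts as significant if its p-value is below 0.025, or if the smaller p-value is below 0.025 and the larger below 0.05.

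| True effects versus control | Power for a given effective regimen | At least one significant | Both significant |
|---|---|---|---|
| One regimen 0.5 SD, the other 0 | 72% | 73% | 3% |
| Both regimens 0.5 SD | 77% | 85% | 68% |

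**Step 4: detectable effect and equivalent size.** Solving the t-test power equation for 80% at 0.025 with n = 64 gives d = 0.5505, and 0.55 × 2.00 = 1.10 points. Holding d = 0.5 instead needs 78 per group: 78 × 3 = 234 evaluable, and 234/0.9 = 260 randomised, against 192 and 213. This shows the size of the gap and is not a recommendation.

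**Step 5: what baseline adjustment could recover.** With baseline-to-6-month correlation ρ, the residual SD shrinks by √(1 − ρ²), so the effective d is 0.5/√(1 − ρ²). Reaching 0.5505 requires 1 − ρ² = (0.5/0.5505)² = 0.825, so ρ is about 0.42. The article gives no ρ, so a range is shown for Holm power per contrast (only that regimen works, then both work):
- ρ = 0: 72% and 77%
- ρ = 0.3: 76% and 81%
- ρ = 0.5: 84% and 88%

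**The case against.** **The article discloses a simplified two-group calculation, and its arithmetic is right.** A reader might infer that 64 is a slip. It is not: 64 reproduces and 213 agrees to rounding. (Writing beta = 0.8 for 80% power mislabels beta, which would be 0.2, but this changes no figure.) What was disclosed, though, is that two groups were compared, not that the planned test is stricter than the one sized.

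**The planned analysis is a linear mixed model, not an unadjusted t-test.** A reader might infer that the trial as analysed must fall short of 80%. The documents do not support that. Baseline values are named among possible covariates, and a moderate correlation would remove the shortfall. Equally, no correlation is stated and none was used in the sizing, so the documents do not show that 80% is reached. This limits the claim to the article's own sizing assumptions.

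**If both regimens work, the chance of at least one significant contrast is 85%.** That is true and belongs beside the other figures. The article does not claim power on that definition, however, and its questions concern specific regimens.

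**Retention may be better than expected.** With all 71 per group evaluable, per-contrast power would be 76% (only that regimen works) to 81% (both work). The article itself plans for 10% loss.

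**The Holm family might be much larger.** Because the Holm sentence follows the 3- and 12-month contrasts, a reader might infer a family of nine: three pairs at three visits. The text argues against this. It tests double versus single at 6 months separately, at 5% and after a gate, and it sets the two 6-month contrasts against control apart as the main outcome. The full membership list may also sit in an analysis plan that is not shown. The two-test family is therefore the one used here.

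**Conclusion.** The point holds as a mismatch between the sizing and the testing rule. The stated 80% belongs to one unadjusted comparison at two-sided 5%. Under Holm with two 6-month contrasts, the same assumptions give about 72% to 77% per contrast, and the effect detectable with 80% power at the first step is 0.55 SD, not the 0.50 SD the article defines as clinically significant.

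These figures assume d = 0.5, 64 evaluable per group, a Holm family of two and no covariate adjustment. The shortfall under the mixed model is unknown and could be nil. Type I error is not in question: Holm controls it over the two contrasts.

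**What to change.** 1. **Sample size {14}.** State that 80% refers to one unadjusted comparison at two-sided 5%. Add that under Holm 64 per group gives about 72% per contrast if only that regimen works and 77% if both work (85% for at least one, 68% for both), or 80% at the first step for 0.55 SD. Alternatively, quote power for the baseline-adjusted model and state the assumed correlation.
2. **Statistical methods {20a}/{20b}.** Say that the Holm family for the primary endpoint is the two 6-month contrasts against control, with the 3- and 12-month contrasts outside it as secondary. Do this before 6-month results by group are seen.
3. **Optional, for the sponsor.** Making single training versus control the one primary contrast at 5%, with double versus control tested next, would fit the first objective and restore the stated 80% for that contrast. It is not required.

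The cost is a few sentences and a slightly less favourable stated figure. No extra participants are needed.

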#### Assessment of clearance from cerebrospinal fluid to blood

A subset of participants from Oslo University Hospital will be included in a sub-study where craniospinal clearance to blood as a surrogate marker of glymphatic function is measured at baseline and after 24 months. The procedure includes a 3 ml injection of Iodixanol 270 mg I/ml (Visipaqueᴿ, GE Healthcare) in the spinal canal by lumbar puncture at the level of L4/L5 using a standardized needle of 22G. We collect plasma 2 and 4 h (±1 h) after intrathecal contrast injection. One aliquot will be used for analysis of Visipaque concentration; the remainder will be stored at −80 °C at Oslo University Hospital pending further analyses.

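### Work package 2 calls the whole-trial sample size adequate for craniospinal clearance, but clearance is measured only in an optional subset at one of five centres, so the statement is not supported for clearance

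*Protocol article*

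**What the plan says.** Protocol article, Sample size {14}: the power estimates rest on "a comparison of two groups with equal sample sizes for simplicity", at 80% power and a 5% significance level. For work package 1, a difference of 0.5 SD is the target, "resulting in a required sample size of 64 participants per group". That makes 192 in three groups, raised to 213 (71 per group) for 10% dropout. No other planned size appears.

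The work package 2 paragraph opens with both factors: "Genetic variation and craniospinal clearance rate may independently influence or modify the effect of working memory training". The next sentence reads "The planned sample size is adequate to detect an effect comparable to the expected intervention effect", again defined as 0.5 SD. It adds: "We should be able to assess possible effect modification within the intervention groups if it is strong", with a Cohen's d of about 1.0. Neither sentence exempts clearance.

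Other sections say who will have a clearance value:

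- Assessment of clearance from cerebrospinal fluid to blood: "A subset of participants from Oslo University Hospital will be included in a sub-study".
- Background and rationale {6a} and Study setting {9}: Oslo is one of five clinics.
- Study setting {9}, recruitment {15} and eligibility criteria {10}: the sub-study has further exclusions, among them age over 80, anticoagulants or two or more antiplatelet drugs, bleeding tendency, renal failure and contrast allergy.
- High responders/subgroups (work package 2): the clearance analysis takes place in the sub-study.
- Adverse event reporting and harms {22}: participants may decline the sub-study, and the clearance investigation is described as exploratory.

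**The concern.** A statement of adequate size made for 213 participants is applied to a variable that most of them will not have. The sample-size section and the sections describing the sub-study cannot both be right about the number available for the clearance analysis.

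The interpretation of a null clearance result is at stake. Finding high responders is a stated aim, and clearance is one of the candidate markers. A reader who relies on the adequacy sentence could take the absence of an association as evidence against an effect of 0.5 SD, when the analysis may have had about a one-in-three chance of detecting it. The primary comparison, the randomisation and the trial size are not affected.

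**Working it through.** **Inputs from Sample size {14}.** Power 80%, alpha 0.05, two equal groups, d = 0.5, 64 per group, 213 in total. Sidedness is not stated. Two-sided is assumed because it reproduces 64.

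**Step 1: reproduce the plan's figure.** Normal approximation: n per group = 2 × (1.96 + 0.84)² / 0.5² ≈ 62.8, so 63. The t-test solution is 63.8, so 64 (power 80.1%). Then 3 × 64 = 192, and 192 / 0.9 = 213.3, stated as 213. The plan's arithmetic reproduces.

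**Step 2: the 0.5 SD statement with the full sample.** For a factor that splits the sample evenly, the two-sample t-test has 93% power at N = 192 and 95% at N = 213. The sentence is true where everyone has a value and the split is even.

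**Step 3: the same statement for clearance.** With N sub-study participants split evenly into high and low clearance, the noncentrality is d × √N / 2 with N − 2 degrees of freedom. The sub-study size is not in the article, so N is an assumption and a range is shown.

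| N with clearance data (assumed) | Power for d = 0.5 | Smallest d at 80% power |
|---|---|---|
| 20 | 19% | 1.32 |
| 30 | 26% | 1.06 |
| 40 | 34% | 0.91 |
| 60 | 48% | 0.74 |
| 100 | 70% | 0.57 |
| 106 (half of 213) | 72% | 0.55 |
| 128 | 80% | 0.50 |

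The requirement is 2 × 64 = 128 evaluable participants: 128 / 213 = 60% of those randomised, or 128 / 192 = 67% of those expected to be evaluable. For orientation only, an equal share per centre would be 213 / 5 ≈ 43 before the extra exclusions and refusals, with 36% power. The article does not say that recruitment is equal across centres.

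**Step 4: does a continuous analysis rescue it?** An even-split difference of d = 0.5 corresponds to r = d / √(d² + 4) = 0.5 / √4.25 = 0.24. By the Fisher transformation, N = (2.80 / atanh 0.24)² + 3, about 132 when r is carried unrounded. The requirement is essentially the same. At N = 40 the detectable correlation is tanh(2.80 / √37) = 0.43.

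**Step 5: the d = 1.0 statement for clearance.** Read as high versus low clearance among trained participants (two thirds of N), power is 70% at N = 40, 81% at N = 51 (34 trained) and 87% at N = 60. Read as a training-by-clearance interaction of 1.0 SD with both training arms against control, SE = √(18 / N). Power is then 32% at N = 40 and 45% at N = 60, and 80% needs about N = 142.

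**The case against.** Several points on the other side stand.

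- **The sub-study size is unknown here.** The article condenses a fuller protocol, and leaving out the size is not in itself a fault. A reader might infer that the claimed sensitivity does not exist at all. The documents do not establish that: the 0.5 SD statement would hold if about 128 evaluable participants came from the sub-study. That is hard to square with an optional, further-restricted subset of one of five centres, but the accurate term is unsupported, not impossible.
- **The d = 1.0 sentence may survive for clearance.** On its literal wording, within the intervention groups, about 51 sub-study participants would suffice (Step 5).
- **The genetic half is not undermined.** Saliva collection carries no site restriction. A reader might infer that the d = 1.0 statement for genotypes has 80% power only near a 50:50 carrier split. The text does not support this. Comparing carriers with non-carriers among trained participants, power is 93% at 25% carriers and 80% at 15% in one arm of 64, and 98% at 15% with both arms. Even as an interaction of both training arms against control it is 81% at 25% carriers. For d = 0.5 at N = 192, power is 93% at an even split, 85% at 25% carriers and 79% at 20%. It falls to 54% at 10%, but the article gives no carrier rates.
- **The consequence is limited.** Clearance is one of many candidate markers in one of four work packages, and the harms section already treats it as exploratory.

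None of this supports the 0.5 SD statement for clearance. The sentence asserts adequacy, names clearance as a subject, and relies on a sample size that other sections withhold from it.

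**Conclusion.** The concern holds for one statement: adequacy to detect 0.5 SD, as applied to craniospinal clearance. It is a mismatch of scope between sections, not an arithmetic error, since 64, 192 and 213 all reproduce. The shortfall depends on an unstated sub-study size, but even half of the whole trial having clearance data would fall short of 80%. The figures assume a two-sided 5% test, an even high/low split and no further loss of evaluable participants; a continuous analysis gives nearly the same requirement. The d = 1.0 statement and the genetic statements are not shown to be wrong. The published sentence should be corrected, but the trial's conduct need not change.

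**What to change.** Split the work package 2 paragraph of Sample size {14}.

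1. Limit the adequacy sentence to genetic variation.
2. For clearance, replace it with the expected number of evaluable sub-study participants and the effect detectable with that number. If it were 40, for example, this would be about 0.91 SD between halves, or a correlation of about 0.43, at 80% power.
3. Label the clearance analysis exploratory or estimation only, reported with confidence intervals, in line with Adverse event reporting and harms {22}.
4. If the d = 1.0 sentence is kept for clearance, say whether it means a contrast among trained participants or a training-by-clearance interaction, and tie it to the sub-study size.

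The cost is one reworded paragraph, with no change to recruitment, measurement or the primary analysis. The downside is that the stated sensitivity for clearance becomes less favourable.
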